## Abstract

**Background:**

While the rates of total knee arthroplasty (TKA) continue to rise worldwide, there are concerns about whether all surgeries are appropriate. Guidelines for appropriateness suggest that patients should have realistic expectations for total knee arthroplasty (TKA), and that the patient and their surgeon should agree that the potential benefits outweigh the potential harms. The objective of this study is to evaluate whether routinely collected pre- and post-TKA patient-reported outcome measures (PROMs) could be integrated into a patient decision aid to better inform these appropriateness criteria. This randomised trial will evaluate the preliminary efficacy of a tailored PROM-based patient decision aid and surgeon report (compared to usual care) for patients considering TKA on decision quality.

**Methods:**

This is a pragmatic, randomised controlled trial conducted at one site in Alberta, Canada. Adults over the age of 30 years, who have been scheduled for a TKA consultation at the Edmonton Bone and Joint Centre with a participating surgeon, who understand, speak, and read English, and can provide informed consent, are eligible to participate. Participants will be randomised to receive a PROM-based patient decision aid and surgeon report before their surgical consultation or usual care. The decision aid will provide patients with information on their expected outcomes based on the EQ-5D-5L PROM, and these estimates are individualized based on clinical and demographic characteristics. The primary outcome of this trial is decision quality. Analysis will consider outcomes intention to treat, and feasibility outcomes for implementing the trial to routine practise.

**Discussion:**

This patient decision aid and surgeon report intervention could contribute to improved treatment decision-making for patients considering total knee arthroplasty.

**Trial registration (registry and number):**

ClinicalTrials.gov: NCT03240913. Registered on August 1, 2017.

## Background

Rates of total knee arthroplasty (TKA) continue to rise worldwide. [1, 2] While TKA reduces pain and disability in a majority of patients, [3] there are concerns about whether all surgeries are appropriate. [3] Six criteria have been endorsed to assess TKA appropriateness. [4] While the surgeon is the best judge for several of these criteria (i.e., the patient has evidence of arthritis on examination; the patient has had an adequate trial of nonsurgical arthritis treatment; the patient is physically and mentally ready to have surgery), two require the elicitation of the patient’s knowledge and preferences. For example, one criterion requires the patient to have “expectations for joint replacement surgery [that] are achievable.” In general, evidence suggests that patients tend to overestimate the potential for benefit of surgery and underestimate the potential for complications. [5] While pre-operative expectations are the strongest predictor of satisfaction with total joint replacement, [6, 7] with as many as one in five patients reporting dissatisfaction with surgery, [7, 8] it can be challenging to elicit patients' expectations. Another appropriateness criterion stipulates that “…the patient and surgeon agree that the potential benefits to the patient of joint replacement surgery outweigh the potential surgical risks.” In order to meet this criterion, patients must be informed about alternatives to TKA and been clear on what matters most to them so they can make informed trade-offs on the relative benefits and risks. Evidence suggests that alternative treatment options, including exercise, education, dietary advice, use of insoles, and pain medication, are not always offered and thus underutilized. [9, 10]

Patient decision aids are interventions that can inform appropriateness criteria for TKA, potentially improving the quality of decisions about appropriate use by supporting shared decision-making between patients and their providers. [11, 12] Patient decision aids in total joint arthroplasty have been found to: increase patient knowledge, result in more realistic expectations, [12, 13] improve patient/provider communication, [14] result in fewer patients having surgery, [12, 13, 15] and be a cost-effective use of resources. [16] While the role of patient decision aids in TKA is promising, there are limitations. Notably, previously developed decision aids are not individualised for each patient, instead relying on average risk information. In addition, they tend to provide information on a narrow set of clinically focussed outcomes (e.g., operative mortality) but not on how treatment will influence outcomes such as pain, which is a clear priority for patients, [17] in addition to mobility, ability to self-care, and ability to participate in activities of daily living [18].

This study seeks to investigate whether the self-reported outcomes of patients who previously underwent TKA can be used to improve decision quality about appropriate use of TKA. Many health systems have been routinely-collecting patient-reported outcome measures (PROMs) pre and post TKA [18–20]. While these data have been collected to support decision-making at a *health systems level,* we believe there is a role for these data to inform setting realistic expectations for patients, and promoting shared decision-making with their care provider. Our preliminary focus group work found that information on ‘average’ patients provided in a decision aid lacked both salience and validity as individuals may perceive that they are different than the average patient (e.g., younger, healthier), and their expectations may truly differ from the average. [21] Moreover, patients were interested in how treatment could impact their day-to-day life - outcomes typically not included in decision aids. [21] Databases of routinely collected PROMs often include more patients than comparable randomised controlled trials, which, when combined with information on demographic and clinical characteristics, may enable outcome estimates to be tailored to the individual. [22] Furthermore, PROMs take the perspective of the patient, and typically represent outcomes that matter more to patients, such as impact on usual activities and self-care, and are described in a language that is easier to understand than clinical measures.

## Methods

The SPIRIT (Standard Protocol Items for Randomized Trials) recommendations guided the development of this protocol. [23] The decision aid was developed according to International Patient Decision Aid Standards (IPDAS). [24]

### Study setting and eligibility criteria

This study is a prospective, single site, two-arm, pragmatic, randomized controlled trial (RCT). It is based at the Edmonton Bone and Joint Centre in Alberta, Canada. In routine practice, patients are referred to the Edmonton Bone and Joint Centre from their primary care provider, or in a minority of cases from a physiotherapist or surgeon. A proportion of patients undergo screening, to determine whether they are eligible for surgery. Candidates for surgery are scheduled for a surgical consultation with an orthopedic surgeon, with most patients waiting 6 to 8 weeks. Most patients receive an appointment reminder letter 3–4 weeks prior to this consultation, which also asks them to complete an online questionnaire at a specified URL (*Routine Questionnaire 1*, Fig. 1). Approximately 30% of participants complete this questionnaire prior to arriving for their consultation, with the remainder completing it while in the waiting room. Following their surgical consultation, patients may be scheduled for surgery (average wait time of 5 to 6 months), or choose not to go on the waiting list. For those that undergo surgery, there is additional data collected on their surgical experience at six-weeks post-surgery (*Routine Questionnaire 2*, Fig. 1) and their outcomes at 3-months post-surgery (*Routine Questionnaire 3*, Fig. 1) and 1-year post-surgery. Currently, there is no follow-up of patients who choose not to have surgery. This study will be integrated into the clinical workflow at the Edmonton Bone and Joint Centre. It aims to evaluate the influence of a PROM-based patient decision aid and surgeon report in patients considering TKA (*decision aid and surgeon report arm*), compared to a control group, which follows routine practice (*no decision aid arm*), on decision quality. Participants will be recruited to the trial following completion of *Routine Questionnaire 1* (Fig. 1), which includes basic demographic information, and information about the affected joint(s). Participants will be excluded if they have not completed the *Routine Questionnaire 1* online prior to the surgical consultation. Patients will be linked to *Study Questionnaire 1* (Fig. 1), which will screen participants for their eligibility. Eligible study participants include: adults over the age of 30 years, who have been scheduled for a TKA consultation at the Edmonton Bone and Joint Centre with a participating surgeon (18 out of 23 surgeons at the clinic), understand, speak, and read English, and can provide informed consent. Patients are excluded if they have had a prior TKA, or have physician-diagnosed rheumatoid arthritis, psoriatic arthritis, ankylosing spondylitis, fibromyalgia or gout. Eligible participants will be informed about the trial via the study-specific web URL that is provided on the appointment reminder letter, and asked to provide online consent. Those consenting to participate will be randomised to either the *decision aid and surgeon report arm* or the *no decision aid arm*. Participants not eligible for inclusion and those who decline consent will follow routine practice.

**Fig. 1 Fig1:**
[figure not shown]
Routine practice and study-specific procedures. PHN: Personal Health Number; h: hip; k: knee; l: left; r: right; QoL: Quality of Life; ABJHI: Alberta Bone and Joint Health Institute; SDM: Shared Decision Making

### Decision aid and surgeon report arm (Fig. 1)

The decision aid and surgeon report arm consists of an online, tailored, PROM-based patient decision aid for the patient and a summary report for the surgeon (Fig. 2). The decision aid has been developed following IPDAS criteria. [24] It is built on existing software which allows information to be tailored to users, and described in a way that promotes higher-quality decision-making. [25] The decision aid includes information about osteoarthritis (OA), which is the primary indication for over 95% of TKAs, and the treatment options available: knee replacement surgery, or other guideline recommended non-surgical treatment (e.g., weight loss, physical therapy, prescription pain medication). [26] These two treatment options are compared across nine aspects that previous qualitative studies have determined to be key factors influencing decision-making. These include the five dimensions from the routinely used EQ-5D PROM related to health-related quality of life (HRQoL): *mobility, self-care, usual activities, pain/discomfort,* and *anxiety/depression,* [27] in addition to: chance of repeat surgery, physiotherapy, recovery period, and risks. Evidence for each aspect comes from both the literature, and data routinely collected in Alberta. Patients are presented with information on: how they compare (pre-surgery) on these five HRQoL dimensions relative to similar patients (based on age, sex, body mass index), and the 3-month post-surgical outcomes of similar patients (based on the above characteristics and baseline HRQoL).

**Fig. 2 Fig2:**
[figure not shown]
Overview of PROM-based decision aid. EQ-5D: EuroQol Questionnaire 5-Dimensions; HK-DQI: Hip and Knee Decision Quality Instrument; CPS: Control Preferences Scale

To date, the Alberta database includes HRQoL data over 6000 individuals who have undergone TKA. The pre-surgery matching algorithm began by searching for more than 50 patients of the same sex, within 5 years of age, and 2.5 body mass index points. These conditions were relaxed in a stepwise fashion until more than 50 matches were found. The pre-surgery information from the matches was presented in 5 separate figures, which allowed patients to compare themselves against similar patients (i.e., am I experiencing more, less, or about the same amount of pain or discomfort as similar patients who undergo surgery?). The post-surgery matching algorithm was completed using the same conditions, in addition to matching patients on self-reported baseline HRQoL. Matching was completed independently for each HRQoL dimension (i.e., there were different number of matches for different dimensions), and results were presented in 5 figures. Figures displayed the outcomes of similar patients 3-months following TKA. For example, patients with ‘moderate pain or discomfort’ at baseline would see the proportion of similar patients who: improved to have no or slight pain or discomfort, continued to have moderate pain or discomfort, or worsened to have severe or extreme pain or discomfort.

The information collected from each participant in the decision aid will automatically generate a summary report for the surgeon, which will be printed by a research assistant in the clinic, and placed in the participant’s file along with an appropriateness checklist. [4] The summary report will be available for viewing by the surgeon during the consultation and the appropriateness checklist will be completed by the surgeon during or after the consultation.

### No decision aid arm (Fig. 1)

The no decision aid arm will follow routine practice. This includes routine data collection, including several PROMs, but no information on OA, treatment options, or potential outcomes. The only deviations from routine practice include the collection of study-specific questions for informing the effectiveness endpoints and the provision of a printed appropriateness checklist in the patients file by a research assistant in the clinic for completion by the surgeon during the surgical consultation.

### Outcomes

#### Primary outcome

The primary outcome for this trial is the difference in the proportion of participants making quality decisions between the two arms. Decision quality is determined to be the key outcome for establishing the effectiveness of decision-making interventions, [11] and is defined as “the extent to which patients are informed and receive treatments that reflect their goals and treatment preferences.” [28] A quality decision requires the patient to: a) be knowledgeable, and b) make a decision that is in concordance with their values. [28] Concordance requires that the patients’ values match with the decision that was implemented, defined as whether the patient had surgery or not at the final assessment. To measure knowledge, we modified one question from the 5-item Hip and Knee Decision Quality Instrument (HK-DQI) related to pain when walking after surgery. In the HK-DQI this question reads, “If 100 people have hip/knee replacement surgery, about how many will have less hip/knee pain when walking after the surgery?” Given the overlap with the EQ-5D-5L dimension of pain or discomfort, and that the decision aid provides tailored estimates of outcomes based on clinical and demographic factors, this question was modified to, “If 100 people like you have knee replacement surgery, how many people improve and have NO or SLIGHT pain or discomfort after surgery?” Individuals getting three or more correct responses (out of five) are considered knowledgeable. Concordance will require that the patient’s treatment preference match their chosen treatment. The following question will measure treatment preference: “Do you feel the potential benefits of knee replacement surgery outweigh the potential surgical risks?” Response options include: “yes,” “no,” and “unsure.” Treatment choice will be ascertained through chart review.

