#### Secondary outcomes

Secondary outcomes are outlined in Table 1 and include those that evaluate preliminary effectiveness of the decision aid, and those related to feasibility of the trial.

**Table 1 Tab1:** Outline of outcomes, instruments, and data collection

	Instrument Name	Source	Baseline (t_0_)	Post-consult (t_1_)	Follow-up (t_2_)
ENROLMENT					
Eligibility screen			X		
Informed consent			X		
Randomization			X		
INTERVENTIONS					
Decision aid plus surgeon report arm (decision aid, surgeon report, appropriateness checklist)			X		
No decision aid arm (appropriateness checklist)			X		
ASSESSMENTS					
Decision quality * Primary Outcome	Modified version of the HK-DQI	[28]			DQ_2_ [K_0_, Pref_0_, Surg_2_]
Demographics (Birthdate, Sex, Joint)			D_0_		
QoL (Generic)	EQ-5D-5L	[29]	E_0_		E_2_
QoL (Condition-specific)	WOMAC	[31]	W_0_		W_2_
Depression	PHQ-9		P_0_		
Knowledge	Modified version of the HK-DQI	[28]	K_0_		
Decisional conflict	SURE	[32]	DC_0_		
Treatment preference		[4]	Pref_0_		
Preference for involvement in decision-making	CPS	[33]	CPS_0_		
Willingness to have surgery			Will_1_		
Patient-reported shared decision-making	CollaboRATE	[34, 35]		C_1_	
Decisional regret	Decision Regret Scale	[36]			R_2_
Satisfaction		[7]			S_2_
Expectations		[7]			EXP_2_
Surgical consult	EMR			Consult_1_	
Surgery	EMR				Surg_2_
Concordance	HK-DQI	[28]			Con_2_ [Pref_0_, Surg_2_]
Feasibility: Recruitment			Recruit_0_		
Feasibility: Questionnaire Completion			Complete_0_	Complete_1_	Complete_2_

QoL: Quality-of-Life; EQ-5D-5L: EuroQol 5-Dimensions Questionnaire (5-level); PHQ-9: Patient Health Questionnaire; WOMAC: Western Ontario and McMaster Universities Arthritis Index; HK-DQI: Hip and Knee Decision Quality Instrument; CPS: Control Preferences Scale; EMR: Electronic Medical Record

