#### Follow-up assessment (t2)

The final follow-up point (3-months post-surgery) will assess a variety of outcomes. For those who had surgery, they will be asked to complete *Routine Questionnaire 3*, while those that did not have surgery will complete *Study Questionnaire 3* at approximately 1 year from baseline (Fig. 1). Both these surveys will assess the patients’ health status (EQ-5D and WOMAC). All participants will then complete *Study Questionnaire 4* (Fig. 1), which assesses patient satisfaction, and some study-specific outcomes including: decisional regret and whether expectations were met. All data collection will be completed through online questionnaires.

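### The concordance part of the primary outcome is worded two ways, and the version Table 1 uses lets waiting-list length decide how some listed patients are scored

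*Protocol article*

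**What the plan says.** All references are to the protocol article.

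- **Primary outcome, performed surgery.** Concordance requires values to "match with the decision that was implemented, defined as whether the patient had surgery or not at the final assessment".
- **Primary outcome, chosen treatment.** Later in the paragraph, concordance requires that the patient's "treatment preference match their chosen treatment", and "Treatment choice will be ascertained through chart review".
- **Preference item.** A single question asks whether benefits outweigh surgical risks. "Response options include: “yes,” “no,” and “unsure". The article gives no scoring for the third answer.
- **Table 1.** The primary outcome is composed as "DQ_2_ [K_0_, Pref_0_, Surg_2" and concordance as "Con_2_ [Pref_0_, Surg_2": baseline preference set against surgery status at follow-up, taken from the electronic medical record.
- **Study setting and eligibility criteria.** After the consultation, "patients may be scheduled for surgery (average wait time of 5 to 6 months), or choose not to go on the waiting list".
- **Follow-up assessment (t2).** Operated patients are assessed 3 months after surgery. The others complete their questionnaire "at approximately 1 year from baseline".

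**The concern.** Choosing surgery and having it are separate events, months apart. For a patient who was listed but has not been operated on, the two sentences give opposite scores, and no rule says which applies. Under the performed-surgery version, the score for such a patient depends on the queue. A 'yes' patient who is listed and waiting fails concordance although preference and choice agree. A 'no' patient who is listed and waiting passes although they disagree.

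The time at which surgery status is read also depends on whether surgery happened, because the final assessment is anchored to the operation for some patients and to baseline for the rest.

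There is a smaller, related gap. Three preference answers have to be matched to two treatments. Read literally, 'unsure' can match neither. Table 2 compares preference between arms as an outcome, so the share of 'unsure' answers may differ by arm, and its scoring could then move the primary result.

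**Working it through.** **1. The two wordings side by side**

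| Preference | Status at about 1 year | Performed-surgery version (Table 1) | Chosen-treatment version |
|---|---|---|---|
| yes | operated | concordant | concordant |
| yes | listed, waiting | discordant | concordant |
| no | listed, waiting | concordant | discordant |
| no | not listed | concordant | concordant |
| unsure | any | not stated | not stated |

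The versions differ only for patients who are listed and still waiting, and the errors run in both directions.

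**2. The plan's own sample size**

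Inputs from Sample size and recruitment: 44.5% against 62%, two-sided 5%, 80% power. The mean proportion is (0.445 + 0.62)/2 = 0.5325. The pooled-variance formula gives

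n = [1.96·√(2·0.5325·0.4675) + 0.8416·√(0.445·0.555 + 0.62·0.38)]² / 0.175² = 126.4, so 127 per arm.

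This reproduces the stated 127, with power 80.2%. The point raised here does not touch that arithmetic.

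**3. How many listed patients would still be waiting at 1 year**

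From the article: the average wait is 5 to 6 months (5.5 used), and the reminder letter is sent 3 to 4 weeks before the consultation. Assumed: baseline falls about 1 month before consultation, so a patient is unoperated at 12 months if the wait exceeds 11 months. The article gives no spread for the wait, so the SD is also assumed.

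| Assumed SD (months) | P(wait > 11), lognormal | P(wait > 11), gamma |
|---|---|---|
| 1.5 | 0.3% | 0.2% |
| 2 | 1.6% | 1.2% |
| 3 | 5.3% | 5.4% |
| 5 | 10.0% | 12.5% |

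Typical surgery falls at about 1 + 5.5 = 6.5 months, well before the 1-year point. Only the long-wait tail is affected.

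**4. Effect on power**

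Assumed: 85% of quality decisions are choices for surgery, and a share f of those patients is still waiting in both arms. Each observed proportion becomes p·(1 − 0.85·f).

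- f = 5%: the multiplier is 0.9575, giving 42.6% against 59.4%, and power at 127 per arm is 76.5%.
- f = 10%: the multiplier is 0.915, giving 40.7% against 56.7%, and power is 72.6%.

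This leaves out the opposite error (listed 'no' patients scored as successes). It also takes the planning rates as free of waiting-list failures.

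**5. 'Unsure', illustration only**

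Suppose decision quality is 55% among decided patients in both arms, and 'unsure' is answered by 20% in one arm and 10% in the other (all assumed). Scored as failures, the arms show 0.55 × 0.80 = 44.0% and 0.55 × 0.90 = 49.5%. With 'unsure' patients excluded, there is no difference.

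**The case against.** The strongest reply is that Table 1 settles the matter. Both the decision-quality row and the concordance row use surgery status at follow-up, and no table uses a listing-based variable. The later sentence can be read as loose wording for the same chart-derived item. This stands to a large extent. A reader might infer two rival primary endpoints, but the article does not support that: the intended variable can be identified, and what remains is a sentence that conflicts with it.

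Second, the article adopts a definition of decision quality that includes the treatment received. Replacing performed surgery by listing would therefore be a trade-off, not the correction of an error. This also stands.

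Third, the follow-up times are questionnaire times, while surgery status comes from the record. In practice the cut-off is near 1 year for most patients, and the average wait ends well before it. This limits the size of the problem but does not supply a fixed date or a rule for those still waiting.

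Fourth, a reader might infer that every 'unsure' patient is counted as a poor decision. The article never says so. It follows only from a literal reading of the matching rule, and an analysis plan not shown may cover it.

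Finally, randomisation gives no reason for waiting times to differ by arm, and the 44.5% planning rate may already contain failures of this kind. If it does, the calculation above counts them twice.

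**Conclusion.** The point holds at moderate severity. The two sentences on concordance need reconciling, and the operational version misclassifies listed-and-waiting patients in both directions because of queue length. The size cannot be derived from the article. The unoperated share runs from about 0.2% to 12.5% across the assumed SDs and the two distributions. At 5% to 10%, power falls from 80% to about 76% to 73%, given the assumed 85% share of surgery choices and an equal loss in both arms.

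A reader might go further and call this a bias that invalidates the primary comparison. The documents do not support that. The waiting-list effect is probably a modest, non-differential dilution, and with short-tailed waits it would be negligible. The 'unsure' gap is secondary. It could act differently by arm, but only if the share of 'unsure' answers differs and no rule exists elsewhere.

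**What to change.** 1. Reconcile the two sentences into one definition of concordance consistent with Table 1.
2. Judge surgery status from the electronic medical record at one fixed time for everyone, for example 12 months from randomisation, whatever the questionnaire date.
3. Count patients listed and still waiting at that time as having chosen surgery. Report the strict performed-surgery version as a sensitivity analysis.
4. State how 'unsure' is scored, with the alternative scoring as a sensitivity analysis. Fix this before allocation is revealed. The Blinding section has analysts unblinded once all surgeon visits are complete, and the baseline preference answers will already exist by then.

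The cost is a few sentences of protocol or analysis-plan wording and one more chart field, listing status. Table 1 names a surgical-consult item from the record but does not say that it captures listing, so the field should be treated as new. The other cost is a small departure from pure treatment received, which the sensitivity analysis keeps visible. No change to visits or sample size is needed.

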### Sample size and recruitment

A previous decision aid trial in hip and knee arthroplasty found that decision quality improved from 44.5 to 56.1% through the use of a patient decision aid and surgeon report. [12] We expect that the current tool will have a greater impact on decision quality through the inclusion of tailored outcome information for each participant based on data from Alberta collected over the past 3 years, rather than presenting average outcome information for all patients. A sample size of 127 participants per arm are needed, to detect an absolute improvement in decision quality of 17.5% (an increase in decision quality from 44.5 to 62%), using a two-sided t-test at the 5% level of significance with 80% power. To account for a 10% loss to follow-up, our target enrolment is 140 patients per arm for a total of sample size of 280. Participants will be recruited from the Edmonton Bone and Joint Centre until the target sample of 280 is achieved. Based on a previous trial run at this centre, [38, 39] we will aim to recruit 40 individuals per month, requiring approximately 7 months to achieve the desired sample size.

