### Statistical methods (Table 2)

The primary analysis evaluating decision quality will be by intention-to-treat. There is no risk of participants in the no decision aid arm receiving the decision aid intervention. However, some participants randomized to the patient decision aid may not complete or engage with the tool in a meaningful way. This includes participants who click through the decision aid without spending sufficient time to read the material. A secondary analysis will assess decision quality while excluding those that do not engage, determined by a minimum of 20 min to complete the decision aid. We will analyze the participants who are lost-to-follow-up using multiple imputation to fully understand the uncertainty due to missing data. Secondary outcomes will be compared as described in Table 2.

**Table 2 Tab2:** Analysis of primary outcome and secondary outcomes

Outcome	Categorical (Cat) Continuous (Con)	Decision aid arm (DA)	No decision aid arm (RP)	Notes
Decision quality	Cat	DQ_2,DA_	DQ_2,RP_	
Quality of Life (Generic)	Con	E_2,DA_ – E_0,DA_	E_2,RP_ – E_0,RP_	
Quality of Life (Condition-specific)	Con	W_2,DA_ – W_0,DA_	W_2,RP_ – W_0,RP_	
Depression	Con	P_2,DA_ – P_0,DA_	P_2,RP_ – P_0,RP_	
Knowledge	Cat	K_0,DA_	K_0,RP_	Modified version of the 5-item HK-DQI
Decisional conflict	Cat	DC_0i,DA_	DC_0i,RP_	Evaluated for each question individually (i = 1–4)
Treatment preference	Cat	Pref_0,DA_	Pref_0,RP_	
Preference for involvement in decision-making	Cat	CPS_0,DA_	CPS_0,RP_	
Willingness to have surgery	Cat	Will_1,DA_	Will_1,RP_	
Patient-reported shared decision-making	Cat Con	C_1,DA_	C_1,RP_	Top-score: complete SDM vs. not complete Mean-score: complete SDM (12) to no SDM (0)
Decisional regret	Con	R_2,DA_	R_2,RP_	
Satisfaction	Con	S_2,DA_	S_2,RP_	Only for those who had surgery
Expectations	Cat	EXP_2,DA_	EXP_2,RP_	Only for those who had surgery
Surgical consult	Cat	Consult_1,DA_	Consult_1,RP_	
Surgery	Cat	Surg_2,DA_	Surg_2,RP_	
Concordance	Cat	Con_2,DA_	Con_2,RP_	
Feasibility: Recruitment	Con	Recruit_0,DA + RP_		Evaluated for the trial and reported as a percentage
Feasibility: Questionnaire Completion	Con	Complete_0,1,2,DA + RP_		Evaluated for the trial and reported as a percentage

HK-DQI: Hip and Knee Decision Quality Instrument; SDM: Shared Decision Making

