Categorical outcomes will be compared between groups using Cochran-Mantel-Haenszel chi-squared tests, with the relative difference in proportions between the decision aid and no decision aid arms calculated as relative risks with 95% confidence intervals. If there is imbalance in covariates previously reported to be associated with surgery uptake, such as age or sex, dichotomous outcomes will be assessed using logistic regression and reported as odds ratios with 95% confidence intervals. We will check the usual statistical assumptions and transform continuous data if necessary. We will use SAS software to fit linear models and use generalized linear models where the assumptions and data distributions are not normally distributed.

Analysis of continuous outcomes will be completed with a 2-sample 2-tailed student’s t-test. As with categorical outcomes, if there is imbalance in key covariates, continuous outcomes will be assessed using linear regression, and if the assumptions do not hold, we will use generalized linear models. Feasibility targets are: a) > 70% recruitment of eligible patients completing their PROMs electronically, and b) > 90% of patients completing study questionnaires.

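### Knowledge is a 0-5 count but is compared between arms only as pass/fail at three correct; a mean-score comparison should be added beside it

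*Protocol article*

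**What the plan says.** Under Primary outcome, the protocol article describes a five-item knowledge measure with one modified item. Its only scoring rule is "Individuals getting three or more correct responses (out of five) are considered knowledgeable". Decision quality then requires a patient to be knowledgeable and to have had the treatment that matches their preference.

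Tables 1 and 2 also list knowledge as a separate outcome, measured at baseline (K_0). Table 2 gives its type as 'Cat' alone, with the note "Modified version of the 5-item HK-DQI". Under Statistical methods, "Categorical outcomes will be compared between groups using Cochran-Mantel-Haenszel chi-squared tests", with relative risks and 95% confidence intervals. For continuous outcomes, "Analysis of continuous outcomes will be completed with a 2-sample 2-tailed student’s t-test". No analysis of the number of correct answers is listed.

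In the same table CollaboRATE, a three-question scale, is typed 'Cat Con', with both a top-score and a mean-score comparison.

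**The concern.** The cut treats 0, 1 and 2 correct as equal, and likewise 3, 4 and 5. Inside the composite that is unavoidable, because each patient must be classed as knowledgeable or not. The separate between-arm comparison does not need it, and there it hides any gain that does not cross from 2 to 3, such as a move from 3 to 5 or from 0 to 2.

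Knowledge is the outcome most directly exposed to the decision aid. The composite also depends on whether surgery took place by the final assessment. If the composite is null or borderline, the knowledge result helps show whether the aid informed patients at all. The article calls the trial a test of preliminary efficacy and proposes a multi-centre study if the primary outcome is met, so an efficient reading of this component is worth having.

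**Working it through.** **The plan's own figure.** Sample size and recruitment gives "A sample size of 127 participants per arm are needed" for "an increase in decision quality from 44.5 to 62" per cent, "using a two-sided t-test at the 5% level of significance with 80% power". With the pooled two-proportion formula,

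n = [1.960·√(2·p̄(1−p̄)) + 0.842·√(p1(1−p1) + p2(1−p2))]² / (p2−p1)²,

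where p1 = 0.445, p2 = 0.62 and p̄ = 0.5325, the result is 126.4, so 127 per arm. The stated figure reproduces (power 80.2% at 127).

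**Number per arm for knowledge.** The 127 is the number after the 10% allowance for loss to follow-up; enrolment is 140 per arm. Knowledge is collected at baseline, before that loss, so 140 is the planned number.

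**Assumptions, since the article gives no knowledge distribution or expected pass rate.**
- The decision-quality effect acts wholly through knowledge.
- Concordance c is the same in both arms and independent of knowledge, so the pass rates are 0.445/c against 0.62/c (planned effect) or 0.561/c (the cited earlier trial).
- The 0-5 score is binomial, with the item probability q solved from P(score ≥ 3) = pass rate.

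**Worked case: c = 100%, planned effect, 140 per arm.**
- Pass/fail: power = Φ{[0.175·√140 − 1.960·√(2·0.5325·0.4675)] / √(0.445·0.555 + 0.62·0.38)} = Φ{(2.071 − 1.383)/0.695} = Φ(0.99) = 83.9%.
- Score: q = 0.4706 and 0.5647, giving means 2.35 and 2.82 and SDs 1.12 and 1.11. Noncentrality = 0.471/(1.11·√(2/140)), about 3.5. Two-sample t-test power = 94.1%.

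**All cases at 140 per arm, two-sided 5%.**

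| Effect | Concordance | Pass rates | Pass/fail power | Mean-score power | Difference, points |
|---|---|---|---|---|---|
| 44.5% to 62% | 100% | 44.5 / 62.0 | 83.9 | 94.1 | 10.3 |
| | 90% | 49.4 / 68.9 | 91.6 | 98.0 | 6.5 |
| | 80% | 55.6 / 77.5 | 97.6 | 99.8 | 2.2 |
| | 70% | 63.6 / 88.6 | 99.9 | 100.0 | 0.1 |
| 44.5% to 56.1% | 100% | 44.5 / 56.1 | 49.2 | 64.0 | 14.7 |
| | 90% | 49.4 / 62.3 | 58.5 | 74.0 | 15.6 |
| | 80% | 55.6 / 70.1 | 71.1 | 86.3 | 15.2 |
| | 70% | 63.6 / 80.1 | 87.3 | 97.4 | 10.1 |

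Differences were taken before rounding.

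**Sensitivity.**
- At 127 per arm the differences are 11.7, 8.1, 3.3 and 0.2 points for the planned effect, and 14.2, 15.5, 16.0 and 12.1 for the smaller one.
- Letting items correlate within a person (beta-binomial, correlation 0.1 to 0.3) barely moves the first case: 10.4 to 10.6 points.
- On a wider grid at 140 per arm (control pass rate 30-80%, difference 10-20 points, item correlation 0-0.5), the median loss is 13 points and the range about 1 to 28. Of the cells, 59% lie between 8 and 16.

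**When the direction reverses.** Start from the binomial control arm with a 44.5% pass rate and move 17.5% of patients from exactly 2 to exactly 3 correct, changing nothing else. The pass rate rises to 62% but the mean rises by only 0.175. Noncentrality = 0.175/(1.12·√(2/140)) = 1.31, so the score has about 26% power against 84% for the cut.

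**The case against.** The strongest defence is that nothing here is misstated. The sentence on three or more correct defines a component of the primary outcome and is right for that purpose. Reporting knowledge and concordance on the definitions used in the composite shows which of them drove it. A rise in score among patients already at three or more cannot change decision quality. This stands, and it means the pass/fail comparison must not be replaced or demoted to a description.

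A second defence is that an extra summary of a secondary outcome can be left to the analysis plan, which is not shown. This stands only in part. Table 2 has a column for outcome type, and the authors filled it in. They gave CollaboRATE two forms and knowledge one, so this is a stated choice. The CollaboRATE row does not oblige every scale to be analysed both ways, but it shows that the format already allows it.

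A reader might infer that the cut costs 8 to 16 points of power across most plausible situations. The documents do not support that. At 140 per arm and the effect the trial was designed for, only full concordance exceeds 8 points, and pass/fail power is at least 84% throughout. The consistently larger losses belong to the earlier trial's smaller effect, and every figure rests on an assumed score distribution.

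**Conclusion.** The point holds as a cheap improvement, not as an error. Knowledge is compared only as pass/fail, and the score information is left unused. Under the stated model at 140 per arm, the cost is about 0 to 10 points of power at the planned effect and about 10 to 16 points at the earlier trial's effect. These figures depend on a binomial score, on the whole effect running through knowledge, and on equal, independent concordance. Other plausible pass rates give losses outside these ranges, and the sign reverses if gains fall mainly between 2 and 3 correct. The article gives no reason to expect that pattern.

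It would be wrong to conclude that the knowledge threshold in the primary outcome is faulty or that the sample size is affected. The threshold is needed there, and the 127 per arm reproduces.

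**What to change.** In Table 2, change the type for Knowledge from 'Cat' to 'Cat Con'. Add a between-arm comparison of the mean number correct (0-5) with a 95% confidence interval, using the t-test or linear regression already planned for continuous outcomes. Keep the comparison of the proportion with three or more correct, because it matches the component of the primary outcome, which is unchanged.

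Make the change before analysts are unblinded. The Blinding section allows this once all surgeon visits are done, so that some secondary analyses can be run, and the baseline knowledge data will have been collected by then.

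The cost is one line in the table or analysis plan and one further secondary comparison to report. No new data, participants or procedures are needed, because scoring the five items already yields the count.
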